#### Data analysis

3.10.2

Prior to analyses, the data will be screened for entry errors and outliers, the extent and type of missing data will be assessed, and the most appropriate method for dealing with the missing data will be selected. For Aim 1, longitudinal cigarette counts (normalized as percent of baseline) will be analyzed using mixed models (Gaussian family) in the primary analysis. The model will include predictors of time (continuous or discrete), study phase (baseline, switch period, or follow-up), flavor group, candidate covariates, and predictors (e.g., e-cigarette use). It will be tested using the z-scores corresponding to the study phase by flavor group interaction terms with fruit-flavored as the reference. For an intent-to-treat (ITT) analyses, ITT will be defined as those randomized to a flavor group at day 6.

For Aim 2, measures are summary scores and difference scores and will be addressed using multiple regression methods. We will first test whether participants randomized to fruit versus tobacco or menthol-flavored e-cigarettes report greater subjective reward, greater increases in positive affect, and have a higher relative reinforcing value of e-cigarette flavoring using the t-score associated with the group difference. We will then test whether these effects predict fewer cigarettes smoked per day during the 6-week switching phase and at the 26-week follow-up.

Next, we will evaluate whether subjective reward, positive affect, and relative reinforcing value for entry into a model as predictors of change in cigarettes smoked per day (mean switch phase or follow-up cigarettes minus mean baseline cigarettes), using the significance of the corresponding t-score while controlling for craving, withdrawal, and negative affect relief. The series of regressions will occur within a structural equation model, with the effects of flavor (predictor) on cigarettes per day (outcome) across the switch follow-up phases mediated by subjective reward, positive affect, and the relative reinforcing value of flavor. We will compute the proportion of mediation for the indirect effects and evaluate the mediated paths for significance using the delta method and bootstrapped standard errors [[68], [69], [70]].

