## Aims and hypotheses

2

The current study (NCT06264154) has two aims. Aim 1 seeks to evaluate the effects of fruit-flavored versus tobacco-flavored and menthol-flavored e-cigarettes on combustible cigarette smoking among adults who have persistently smoked. We hypothesize that participants randomized to fruit-flavored e-cigarettes will be more likely to switch from combustible cigarettes to e-cigarettes during the 6-week switch phase and at the 26-week follow-up than participants randomized to tobacco-flavored or menthol-flavored e-cigarettes. Complete switching, partial switching, and no switching will be measured. Aim 2 seeks to examine whether the rewarding and reinforcing effects of e-cigarette flavoring mediate switching behavior. We hypothesize that fruit-flavored e-cigarettes will produce greater subjective reward, relative reinforcing value, and positive affect than tobacco-flavored or menthol-flavored e-cigarettes. In turn, greater subjective reward, relative reinforcing value, and positive affect will predict fewer cigarettes smoked per day during the 6-week switch phase and at the 26-week follow-up.

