#### Sample size

3.10.1

For Aim 1, hypotheses will be tested with 80% power using 5% two-sided alpha Bonferroni corrected to 2.5% for two group comparisons. The primary outcome is the longitudinal daily cigarette count from baseline (days 1-5) to the end of the e-cigarette switch phase (day 49), with week 26 as a secondary endpoint. We based the power on data from prior switching studies. A sample of 210 (70 per group) will allow us to detect an overall standardized slope of 0.19. To account for a ∼15% attrition rate [67], we will enroll ∼ 240 participants to have 210 who complete the 26-week follow-up. We expect the initial and sustained switch for participants randomized to fruit-flavoring to be greater than for participants randomized to tobacco or menthol flavoring. A sample of 70 per group enables us to detect a difference of ∼3.73 cigarettes per day (CPD). We will also be able to detect a difference in slopes of 0.13 (CPD per day change).

For Aim 2, a sample of 70 per group will allow us to detect a between-group effect size of 0.5. For the relative reinforcing value of flavored e-cigarettes (RRVF), this means we can detect a difference in breakpoint of 2.0. Positive affect will be assessed as a difference score with a standard deviation of approximately 7.0, yielding 80% power to detect a difference of approximately 3.7. Subjective reward has a standard deviation of 1.3, which allows us to detect a 0.68 difference. In turn, the continuous measures of RRVF, positive affect, and subjective reward will be used to predict changes in mean cigarette counts from baseline to the end of the switch phase and from baseline to the 26-week follow-up. The sample of 210 allows us to detect a standardized slope of 0.2. The actual standard deviation for the cigarette consumption change score is 7.1. The detectable slopes are 0.37 for RRVF, 0.20 for positive affect, and 1.07 for subjective reward.

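### Aim 1 tests flavor on percent of baseline smoking, but Aim 2 mediates raw change in cigarettes per day, so the proportion mediated refers to a total effect on a different scale

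*Protocol article*

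**What the plan says.** All of this is in the protocol article.

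- **Aim 1 model (3.10.2 Data analysis).** "longitudinal cigarette counts (normalized as percent of baseline) will be analyzed using mixed models (Gaussian family) in the primary analysis". The flavor effect is "tested using the z-scores corresponding to the study phase by flavor group interaction terms with fruit-flavored as the reference".
- **Aim 2 regressions (3.10.2).** The mediators are entered as predictors of "change in cigarettes smoked per day (mean switch phase or follow-up cigarettes minus mean baseline cigarettes", a raw difference in cigarettes per day.
- **Aim 2 structural equation model (3.10.2).** It models "the effects of flavor (predictor) on cigarettes per day (outcome) across the switch follow-up phases mediated by subjective reward, positive affect" and relative reinforcing value. The summary is then "We will compute the proportion of mediation for the indirect effects".
- **Purpose of Aim 2 (section 2).** "Aim 2 seeks to examine whether the rewarding and reinforcing effects of e-cigarette flavoring mediate switching behavior". The Conclusions (4.2) likewise promise to show whether fruit flavor helps switching and why.
- **Planning (3.10.1 Sample size).** "The primary outcome is the longitudinal daily cigarette count from baseline (days 1-5) to the end of the e-cigarette switch phase (day 49", with no mention of percent of baseline. The Aim 1 detectable effects are 3.73 CPD and 0.13 CPD per day. The Aim 2 slopes rest on a change-score SD of 7.1 CPD.

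Nothing in the article links the two scales or plans either analysis on the other one.

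**The concern.** Aim 2 is presented as explaining the switching that Aim 1 tests. A proportion mediated is the indirect effect divided by the total effect, so it is only as relevant to Aim 1 as its denominator is. Here the denominator is a flavor difference in mean raw CPD change, which the Aim 1 primary model does not estimate.

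Percent of baseline gives each participant's proportional reduction the same weight. Raw change multiplies that reduction by baseline consumption, so heavier smokers count for more. Entry requires at least 5 CPD with no stated upper limit (3.2), so the weights can differ widely.

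At stake is the trial's explanatory statement. A share computed on raw CPD could be reported as the share of the percent-of-baseline effect, and the mediation analysis would run on the noisier outcome.

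**Working it through.** **1. Which scale the planning uses.** The inputs from 3.10.1 are 70 per group, 80% power, two-sided alpha 0.025 after Bonferroni, and SD 7.1 CPD. For a two-sample t comparison with 138 degrees of freedom, the detectable standardized difference is 0.526.

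- Aim 1: 0.526 × 7.1 = 3.73 CPD, which matches the stated figure.
- Aim 2: slope = standardized slope × 7.1 / SD of the mediator. The stated 0.2, taken as 0.196 before rounding, gives 0.196 × 7.1 / 7.0 = 0.20 for positive affect and 0.196 × 7.1 / 1.3 = 1.07 for subjective reward. For relative reinforcing value the implied SD is 2.0 / 0.526 = 3.80, and 0.196 × 7.1 / 3.80 = 0.37. All three match.

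So the planning for both aims and the Aim 2 outcome are on raw CPD. Only the Aim 1 model is on percent of baseline.

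**2. How the two effects relate.** Let B be baseline CPD, P the fraction of baseline smoked later, and τ(B) the flavor difference in mean P at baseline level B. Percent of baseline is 100·P and raw change is B·(P − 1). Under randomization:

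- percent-scale effect = 100 × E[τ(B)]
- raw-scale effect = E[B·τ(B)] = E[B]·E[τ(B)] + Cov(B, τ(B))

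The raw effect is a fixed multiple, E[B], of the proportional effect only when the covariance term is zero, which holds when τ does not vary with baseline.

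Two equal strata at 6 and 30 CPD (assumed; mean 18) show the difference:

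| Fruit benefit, light / heavy smokers | Percent scale | Raw scale |
|---|---|---|
| 20 / 20 points | −20 points | −(0.2×6 + 0.2×30)/2 = −3.6 CPD, which is 20% of 18 |
| 50 / 0 points | −25 points | −(0.5×6 + 0×30)/2 = −1.5 CPD, against 25% of 18 = 4.5 |

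**3. Effect on the proportion mediated.** This is an illustrative simulation of 400,000 participants with assumed inputs: lognormal baseline with median 14 CPD, limited to 5–60, and one mediator shifted by 0.52 SD.

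| Setting | Percent scale | Raw scale |
|---|---|---|
| Proportional effect constant over baseline | 0.34 | 0.35 |
| Direct effect larger in heavy smokers | 0.34 | 0.27 |
| Direct effect smaller in heavy smokers | 0.34 | 0.45 |
| Direct effect much smaller in heavy smokers | 0.34 | 0.66 |

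**4. Effect on precision when the proportional effect is constant.** This is a simulation of 3,000 trials per setting, 70 per arm, two-sided 2.5%. The assumptions are a lognormal baseline with mean 12 to 16 CPD, SD half the mean and floor 5; controls at 45% of baseline; fruit 10 to 20 points lower; and fraction smoked drawn from a Beta distribution with concentration 1.6. The raw-change SD came out at 5.2 to 7.0, close to the article's 7.1 at the upper end.

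| Outcome for the flavor test | Power at a 15-point difference |
|---|---|
| Percent of baseline | 75–78% |
| Raw change | 38–43% |
| Raw change with baseline CPD entered | 64–68% |

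Across the 10- to 20-point effects, percent was significant and raw change was not in 22% to 39% of trials, or 4% to 13% with baseline CPD entered.

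**5. What cannot be computed.** The article gives no SD for percent of baseline and no mean baseline CPD. If mean baseline is 10, 15, 20 or 30 CPD, 3.73 CPD is 37.3, 24.9, 18.7 or 12.4 points of baseline.

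**The case against.** The strongest reply is that Aim 2 is coherent within itself. Its hypothesis in section 2, its planning figures and its analysis are all in cigarettes per day, and its proportion mediated has its own denominator inside its own model. This stands. The fault lies between the aims, and the scale that departs from the rest is that of the Aim 1 model.

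It can also be said that the share attributed to reward hardly moves (0.34 versus 0.35) when flavor acts by the same proportion at every baseline. This stands too. The discordance rates in step 4 come from that constant-effect case and contain no mediator, so they measure lost precision and do not show a different explanation. Table 1 lists baseline CPD as a covariate. Entering it recovers much of the loss, although 3.10.2 does not say that it enters the Aim 2 model.

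Three stronger readings are tempting, and the article does not support them.

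- A reader might infer that a significant Aim 1 result could leave Aim 2 with nothing to mediate. Section 3.10.2 judges the mediated paths by the delta method and bootstrapped standard errors and requires no significant total effect.
- A reader might infer that direct plus indirect effects ought to add up to the Aim 1 estimate. The article does not promise this, and a shared scale would not achieve it. Aim 1 is a mixed model on repeated counts with its own covariates. Aim 2 uses a single mean change and controls for craving, withdrawal and negative affect relief.
- A reader might infer that the two effects could point in opposite directions. In the two-stratum example that needs a 40-point benefit in light smokers and a 10-point harm in heavy smokers (−15 points, +0.3 CPD). Nothing in the article suggests such a pattern.

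**Conclusion.** The mismatch is stated in the text of 3.10.2 and is not a detail left to an analysis plan. As written, the mediation analysis explains an effect on raw CPD change, while the trial tests an effect on percent of baseline.

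How much this shifts the proportion mediated depends on whether flavor's proportional effect varies with baseline smoking, which the article does not quantify. In the illustrations the shift ran from negligible (0.34 versus 0.35) to large (0.34 versus 0.66). The loss of precision does not need such variation: 38–43% power on raw change against 75–78% on percent, narrowing to 64–68% with baseline CPD entered. All these figures rest on assumed baseline distributions, control levels and effect sizes. The validity of the Aim 1 test is untouched. The point concerns the mechanistic aim and how its result may be described.

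**What to change.** - Use the Aim 1 outcome scale for the Aim 2 regressions and structural equation model, at the switch phase and at week 26. Keep the other scale as a paired sensitivity analysis.
- If raw change is kept for Aim 2, enter baseline CPD in those models and also report the Aim 1 flavor contrast on raw CPD, so that the total effect being mediated has been reported.
- Restate the planning figures on the chosen scale. If percent is kept, this covers the three Aim 2 slopes and also the Aim 1 figures of 3.73 CPD and 0.13 CPD per day. If raw CPD is chosen for both aims, these figures are already on that scale and the Aim 1 model is what changes.
- State that a shared scale makes the mediation refer to the tested effect, without implying that its components will sum to the mixed-model estimate.

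The cost is revised wording, one extra set of analyses and restated planning figures. Keeping percent needs a percent-scale SD from the prior switching data. No new trial data or visits are needed.

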### Assessments

3.8

Table 1 summarizes the measured variables and their measurement time points. Covariates will include demographics, smoking history, e-cigarette use history, marijuana use, nicotine dependence as measured by the Fagerstrom Test for Nicotine Dependence [47], the modified Penn State Dependence Scale [48], carbon monoxide measured with iCO quit (Bedfont Scientific), depression symptoms measured with the 20-item Center for Epidemiological Studies - Depression scale [[49], [50], [51]], and anxiety measured with the Generalized Anxiety Disorder-7 [52,53].

**Table 1 tbl1:** Schedule of study measures.

Measures	Laboratory Visits				
	Baseline	Day 6	Day 7	Weeks 2-7	Week 26

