**Predictor Variables**					
Craving Relief		X			
Withdrawal Relief		X			
Negative Affect		X			
ECIG pods per day				XXXXXX	X

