**Outcome Variable**					
Cigarettes per day				XXXXXX	X

Predictor variables will include craving, measured by the 10-item Brief Questionnaire of Smoking Urges [54,55]; withdrawal symptoms, assessed with the Minnesota Nicotine Withdrawal Scale [56,57]; and negative affect, evaluated using the Positive and Negative Affect Schedule [[58], [59], [60]]. Additionally, e-cigarette use will be recorded by counting the daily e-cigarette pods returned over each of the 42 days of the switch period (days 8–49) [32,35,61]. The total number of pods used during the switch phase will be determined by summing fully and partially used pods. Partially used pods will be weighed and converted into a fraction of a pod used [61].

Mediating variables include the subjective rewarding value of e-cigarette flavor, measured with the Satisfaction Subscale of the modified Cigarette Evaluation Questionnaire adapted for e-cigarette use [23,[62], [63], [64]]; positive affect measured with the Positive and Negative Affect Schedule [[58], [59], [60]], and the relative reinforcing value of flavor measured with a validated computer-based choice paradigm, which evaluates the preference for flavored e-cigarette puffs versus cigarette puffs [37,65].

The primary outcome is the longitudinal daily count of cigarettes from baseline to the end of the e-cigarette switch phase. Daily cigarette consumption will be determined by counting the daily spent cigarette filters returned for each of the 42 days (days 8 – 49) [32,35]. Cigarette smoking behavior at the 26-week follow-up will serve as a secondary endpoint. Average CPD at the 26-week follow-up will be measured via a valid and reliable TLFB procedure [66]. A CO value < 5 ppm will verify combustible cigarette abstinence (complete switching) at these time points.

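### The primary Aim 1 model is to adjust for e-cigarette use measured after randomisation; if use enters as a time-varying term, the phase-by-flavor test no longer estimates the total effect of assigned flavor

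*Protocol article*

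**What the plan says.** Section 3.10.2 says that the longitudinal cigarette counts "will be analyzed using mixed models (Gaussian family) in the primary analysis". Besides time and study phase, that model is to include "flavor group, candidate covariates, and predictors (e.g., e-cigarette use"). The next sentence fixes the test: "It will be tested using the z-scores corresponding to the study phase by flavor group interaction terms with fruit-flavored as the reference". No primary model without e-cigarette use is described.

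Section 3.8 defines the variable: "e-cigarette use will be recorded by counting the daily e-cigarette pods returned over each of the 42 days of the switch period (days 8–49"). Table 1 lists "ECIG pods per day" under Predictor Variables, with entries at weeks 2–7 and week 26 and none at baseline. Prior e-cigarette history is a separate item: "Covariates will include demographics, smoking history, e-cigarette use history, marijuana use, nicotine dependence".

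The Introduction argues that fruit flavors are vaped more often and more deeply than other flavors, and that e-cigarettes can substitute for cigarettes when they are comparably reinforcing. Section 2 frames Aim 1 as a comparison of participants by the flavor to which they are randomised.

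**The concern.** Pod use is an outcome of randomisation, and the Introduction places it between flavor and smoking. A model that holds it fixed asks whether fruit reduces smoking beyond the vaping it induces. Aim 1 asks a different question: what assignment to fruit does to smoking.

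Two kinds of error can follow. If fruit works partly by getting people to vape more, the tested term shrinks and a real effect may be missed. If something such as nicotine need drives both pod use and smoking, conditioning on pods breaks the balance that randomisation gave, and an effect can appear where there is none.

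The Discussion says that an unsupported hypothesis would suggest that fruit flavors confer no advantage and that their absence from the market does no harm to adults who want to quit this way. A null produced by over-adjustment would be read in the same way.

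**Working it through.** **Inputs from the protocol (Section 3.10.1):** 70 per group; difference 3.73 CPD; two-sided alpha 2.5% per comparison; power 80%. The SD of 7.1 for the change in cigarettes is stated under Aim 2 and is assumed here to apply to Aim 1.

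**Assumed, because the protocol gives no value:** the share s of the effect that passes through pods, the pod–cigarette association, and the strength of any shared cause.

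**Step 1. Reproduce the plan.** The standard error of a difference is 7.1 × √(2/70) = 1.200.
- Detectable difference: 1.200 × (2.241 + 0.842) = 3.70 CPD, against 3.73 stated.
- Sample size: 2 × (7.1 × 3.083 / 3.73)² = 68.9, so 69 per group, against 70 stated.
- Power: Φ(3.73/1.200 − 2.241) = Φ(0.867) = 0.807.

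The stated figure is thus reproduced by an unadjusted comparison of groups, that is, by the total effect of flavor.

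**Step 2. Adjust for pods.** The coefficient left for flavor is (1 − s) × 3.73. Its power was found in three ways: by the formula in step 1 with the smaller difference, and by two simulations of a two-arm regression on change scores. Simulation A assumes a pod–cigarette correlation of −0.4. Simulation B assumes −5 CPD per pod per day and a pod SD of 0.4, a correlation of −5 × 0.4 / 7.1 = −0.28. The pod shift that flavor must cause is s × 3.73 / (0.4 × 7.1) SD in A and s × 3.73 / (5 × 0.4) SD in B.

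| Share s | (1 − s) × 3.73 | Power, formula | A: estimate, power | B: estimate, power | Pod shift needed, A / B |
|---|---|---|---|---|---|
| 25% | 2.80 | 54% | 2.8, 59% | 2.85, 56% | 0.33 / 0.47 SD |
| 50% | 1.87 | 25% | 1.9, 25% | 1.87, 22% | 0.66 / 0.93 SD |
| 75% | 0.93 | 7% | 1.0, 7% | 0.89, 5% | 0.99 / 1.40 SD |
| 100% | 0 | – | 0.0, 2% | 0.01, 2% | 1.31 / 1.87 SD |

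Unadjusted power stayed near 80% throughout.

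**Step 3. Add a shared cause.** Suppose an unmeasured factor raises both pod use and smoking.
- With no flavor effect on smoking, a 0.5 SD flavor effect on pods and loadings of 0.5, the bias is 0.5 × 0.5 × 0.5 × 7.1 = 0.89 CPD in favor of fruit. Type I error was 7.5%.
- With a pod shift of 0.3 per day (0.75 SD) and stronger shared causes, the bias was 1.1 to 1.9 CPD and type I error 8% to 24%. The unadjusted test stayed at 2.2% to 2.6%.
- With a real effect of 3.73 CPD, the smaller of those two shared causes partly offsets the shrinkage in B: 3.50 CPD and 70% power at s = 25%, 3.24 CPD and 58% at s = 50%.

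**Step 4. Does the form of the term matter?** One large simulated data set (400 per arm, half the effect through pods) was fitted with mixed models containing a phase-by-group interaction. The interaction was −4.12 without pods, −2.39 with pods as a time-varying term, and −4.12 with each person's pod level as a constant main effect.

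**The case against.** The strongest reply is that the protocol does not say how e-cigarette use enters the model. As step 4 shows, a constant person-level main effect would do no harm to the interaction. This stands as a limit on the point. Even so, pods are counted daily, no study pods are given out before day 7, and regular e-cigarette users are excluded. In a longitudinal model that includes the baseline phase, the obvious use of such data is a time-varying term.

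The word candidate might also be read as covering the predictors, so that use would only be screened for entry. That is the weaker reading of the sentence, and a data-driven choice to include a post-randomisation variable would carry the same risk.

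Three stronger claims are tempting, and the document does not support them.
- A reader might infer that the Day 6 craving, withdrawal and negative-affect measures are also in the Aim 1 model, because Table 1 files them under the same label. Section 3.10.2 names only e-cigarette use for Aim 1 and places those measures as controls in Aim 2.
- A reader might see a contradiction with intention to treat. The sentence "ITT will be defined as those randomized to a flavor group at day 6" fixes who is analysed and says nothing about model terms, so there is no contradiction in the text. Nor does it cure the problem, since analysing everyone randomised does not protect the contrast once a mediator is held fixed.
- A reader might quote the 7% and 2% power rows as the expected loss. They need flavor to move pod use by about 1 SD or more. With a 0.5 SD shift and a correlation of −0.4, the share is 0.5 / 1.31 = 38%, the estimate about 2.3 CPD and power about 42%.

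The illustration is also simpler than the planned analysis. It compares CPD change between two arms, whereas the plan models percent of baseline over time. It shows direction and rough scale only.

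**Conclusion.** The point holds in a conditional form. As written, the primary model includes a variable measured after randomisation that lies on the path from flavor to smoking. If it is time-varying, the primary interaction does not estimate the total effect that Aim 1 asks about and that the 3.73 CPD calculation appears to power.

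At mediated shares of 25% to 50% with no shared cause, the loss is about 0.9 to 1.9 CPD of a 3.73 CPD effect, and power drops from about 80% to somewhere between 59% and 22%. A shared cause can offset some of this loss, but it can also produce false positives. Neither the size nor the net direction can be fixed from the document, because the shares, associations and loadings are assumptions. The sensitivity analyses in Section 3.10.3 vary only the handling of missing data, so none of them would reveal the problem. Because it affects the primary test, it should be settled before that test is run.

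**What to change.** In Section 3.10.2, remove the predictors, and with them the e-cigarette use example, from the list of terms in the primary Aim 1 model. State that the model contains time, study phase, flavor group, the phase-by-flavor interaction and covariates measured before randomisation, and nothing else. Carry the same wording into the statistical analysis plan.

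If a model that adjusts for pods per day is wanted, report it separately, label it exploratory, and state how pods enter. The Aim 2 mediation model, with its three prespecified mediators, need not change.

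The cost is a sentence or two of text. No data, visits or participants are affected, and the stated sample size stands.

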### Overview of study design

3.1

The proposed study will evaluate whether fruit-flavored (FF: watermelon and blueberry) versus traditional-flavored e-cigarettes [tobacco (TF) or menthol (MF)] more readily substitute for combustible cigarettes and if the rewarding and reinforcing effects of flavoring facilitate changes in smoking behavior among 210 adults who have persistently smoked cigarettes. Eligible adults will be randomly assigned 1:1:1 to FF (n = 70), TF (n = 70), or MF (n = 70) and participate in 9 visits across 26 weeks (see Fig. 1). Baseline cigarette smoking rate will be established over days 1-5. After overnight smoking abstinence, a laboratory visit on day 6 will assess e-cigarette flavor-associated subjective reward, affect, craving relief, and withdrawal relief. After overnight smoking abstinence, a laboratory visit on day 7 will assess the reinforcing value of the assigned e-cigarette flavor relative to combustible cigarettes.

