#### Flavor-associated subjective reward and positive affect (Day 6)

3.5.1

Participants will attend a laboratory session after overnight smoking abstinence (10 h; CO verified <10) on day 6 [23,34]. Cigarette craving, withdrawal symptoms, and positive and negative affect will be measured before e-cigarette exposure. They will receive instructions on how to use the e-cigarette before two e-cigarette exposures based on their flavor group assignment. On day 6, the traditional flavor groups will receive either two exposures of tobacco or two exposures of menthol flavoring, depending on their assignment. The fruit flavor group will receive blueberry and watermelon in a counterbalanced order. All exposures will have the same characteristics, only differing by flavor. Participants will take 14 puffs for the first exposure and 14 puffs for the second exposure. The exposures will be separated by 45 min [23,35]. After each exposure, participants will complete measures of subjective reward, craving, withdrawal, and affect. We chose to offer both watermelon and blueberry to participants randomized to fruit-flavored e-cigarettes to promote adherence if either flavor was unappealing. After this 1.25-h visit, participants will be compensated $40.

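### Aim 2 scores positive affect as a difference score and names no adjustment for the pre-exposure value collected on Day 6: forgone efficiency, and a mediator that can carry starting affect level

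*Protocol article*

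**What the plan says.** Section 3.5.1 (Day 6 laboratory visit) collects the baseline: "Cigarette craving, withdrawal symptoms, and positive and negative affect will be measured before e-cigarette exposure". It then collects the response: "After each exposure, participants will complete measures of subjective reward, craving, withdrawal, and affect". There are two exposures, and the article does not say how the two post-exposure scores are combined.

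Section 3.10.1 fixes the scoring: "Positive affect will be assessed as a difference score with a standard deviation of approximately 7.0", with 80% power for a difference of about 3.7.

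Section 3.10.2 places Aim 2 under multiple regression on summary and difference scores. The first-stage question is whether participants given fruit flavor "report greater subjective reward, greater increases in positive affect, and have a higher relative reinforcing value of e-cigarette flavoring using the t-score associated with the" between-group contrast. The mediators then predict change in cigarettes per day, controlling for craving, withdrawal and negative affect relief. The whole set is fitted as a structural equation model that yields indirect effects and a proportion mediated.

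Pre-exposure positive affect does not appear in the covariate list of section 3.8 or in that control set.

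**The concern.** Positive affect is one of three hypothesized mediators. A difference score subtracts the pre-exposure value with a coefficient fixed at 1, whereas a regression on that value estimates the coefficient from the data. Two things are at stake.

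- **First stage (flavor to affect).** Unless the true within-group slope of post on pre is 1, the difference score leaves variance that the pre-exposure value would explain. The standard error is larger than it need be. A chance imbalance in starting affect also moves the observed group difference.
- **Second stage (affect to cigarettes).** Participants are not randomized to their affect response. If the change score is correlated with starting affect, and starting affect after overnight abstinence is related to later smoking, the mediator coefficient mixes response to flavor with starting level. That coefficient enters the indirect effect and the proportion mediated, on which Aim 2's account of why flavor works depends.

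**Working it through.** **Inputs from the protocol article.** SD of the difference score 7.0; detectable difference 3.7; 80% power; 70 per group (section 3.10.1); 1:1:1 allocation (section 3.1). The alpha is stated for Aim 1: "hypotheses will be tested with 80% power using 5% two-sided alpha Bonferroni corrected to 2.5% for two group comparisons". None is stated for Aim 2, so both levels were tried.

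**Step 1: reproduce the plan's figure.** Unadjusted two-sample comparison of the change score:

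detectable difference = (z for alpha/2 + z for power) × SD × √(2/n)

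- Two-sided 2.5%: (2.241 + 0.842) × 7.0 × √(2/70) = 3.65 (3.68 with the noncentral t). Power at 3.7 is 80.4% (noncentral t).
- Two-sided 5%: 3.31. Power at 3.7 is 87.4%.

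The stated 3.7 matches the 2.5% version with no adjustment. The planned power therefore takes no credit for the baseline value.

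**Step 2: effect of adjusting.** Let the pre-exposure SD be s, the post-exposure SD be k·s, and the pre-post correlation be rho.

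- Variance of the change score: s²(1 + k² − 2·rho·k)
- Residual variance after adjustment: s²·k²(1 − rho²)
- Difference between them: s²(1 − rho·k)²

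This difference is never negative, and it is zero only when rho·k = 1. With equal variances (k = 1), the ratio of residual to change-score variance is 2(1 − rho)(1 + rho)/2 divided by 2(1 − rho), that is (1 + rho)/2. The adjusted SD is then 7.0 × √((1 + rho)/2). Neither rho nor k is in the documents, so a range is shown for a 3.7-point difference at two-sided 2.5%. Power is by noncentral t; detectable differences use the normal approximation.

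| rho (assumed, k = 1) | adjusted SD | power | gain over 80.4% | detectable difference (unadjusted 3.65) |
|---|---|---|---|---|
| 0.5 | 6.06 | 90.9% | 10.5 points | 3.16 |
| 0.7 | 6.45 | 86.9% | 6.4 points | 3.36 |
| 0.8 | 6.64 | 84.7% | 4.3 points | 3.46 |
| 0.9 | 6.82 | 82.6% | 2.1 points | 3.56 |

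Sensitivity:
- If k exceeds 1 the gain falls as rho·k approaches 1. At rho = 0.75 and k = 4/3 the product is 1 and there is no gain.
- If the post value is the mean of the two exposures, the gain is about 5 to 13 points over the combinations tried (rho 0.5 to 0.8).
- At two-sided 5% the gain is about 3 to 7 points for rho 0.8 to 0.5.

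**Step 3: chance imbalance.** With k = 1, s = 7.0/√(2(1 − rho)), and the slope of change on baseline is −(1 − rho). A one-standard-error imbalance, s × √(2/70), shifts the unadjusted difference by:
- rho 0.5: s = 7.0; 7.0 × 0.169 × 0.5 = 0.59 points
- rho 0.7: s = 9.0; 9.0 × 0.169 × 0.3 = 0.46 points
- rho 0.8: s = 11.1; 11.1 × 0.169 × 0.2 = 0.37 points (computed before rounding s)

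**Step 4: mediator path.** With k = 1, the correlation of change with baseline is −√((1 − rho)/2): −0.50 at rho 0.5, −0.39 at 0.7 and −0.32 at 0.8. Suppose the response to flavor has no effect on smoking, but starting affect correlates with smoking change at r (an assumption; no value is given). Before any other control, the change score then shows a standardized slope of size r times that correlation:
- r = 0.1: 0.03 to 0.05
- r = 0.2: 0.06 to 0.10
- r = 0.3: 0.10 to 0.15

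Section 3.10.1 gives 0.2 as the standardized slope that the trial can detect for this path.

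**The case against.** The strongest reply is that nothing in the article rules out adjustment. Multiple regression leaves room for covariates, the t-score for the group difference could come from an adjusted model, and a condensed article may leave the covariate set to the full protocol or analysis plan. Regressing the change score on group plus the pre-exposure value gives the same group effect as modeling the post value, so the stated scoring is compatible with the fix. Planning on an unadjusted SD is a common conservative convention and does not prove that the analysis is unadjusted.

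This stands as far as it goes. A reader might infer that the plan has decided against adjustment; the documents do not say so. What they show is a difference score, an explicit control set for the mediator model, and no mention of the pre-exposure value in either. Naming a covariate already in hand improves on that published choice.

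Three stronger readings are also unsupported.
- **That the comparison is biased or invalid.** Under randomization the change-score comparison is unbiased on average with correct type I error, and regression to the mean acts alike across arms in expectation. Imbalance matters only conditionally on what is observed, and stratification by depression/anxiety (section 3.4) may limit it.
- **That the trial is short of power here.** It reaches its stated 80% without adjustment.
- **That a fixed number of power points is lost, or that change must correlate negatively with baseline.** Both depend on rho and on the ratio of the SDs. Pre and post scores come from one 1.25-hour visit, so a high rho and a small gain cannot be excluded.

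Change in positive affect is also a defensible mediator in itself, since the hypothesis concerns increases, and the outcome model already controls for three relief measures. Those measures may absorb part of the starting-level effect. None of them is pre-exposure positive affect.

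**Conclusion.** The point holds as a recommended improvement, not as an error that invalidates Aim 2. The article fixes a post-minus-pre difference score and names no adjustment for the pre-exposure value, in either the flavor-to-affect regression or the mediator model. For the group comparison the cost is forgone efficiency of about 2 to 10 power points for rho from 0.9 to 0.5, under equal variances, one post value and two-sided 2.5%. It could be nil if post-exposure variance is sufficiently larger.

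The mediator path is the more material part, because randomization does not protect it. Under equal variances, a correlation of −0.50 to −0.32 between change and starting affect (rho 0.5 to 0.8) can pass into the indirect effect and the proportion mediated. How much passes depends on how strongly starting affect relates to smoking, which the documents do not give.

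All of this takes the pre-exposure score to be unaffected by flavor assignment. Allocation is unblinded, and the article does not say whether participants know their flavor when that score is taken.

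**What to change.** In section 3.10.2:
- Include pre-exposure Day 6 positive affect as a covariate in the regression of positive affect (post value or change) on flavor group.
- Include it in the positive-affect mediator equation of the structural equation model, and in that mediator's path to cigarettes per day.
- Report the group effect in points on the Positive and Negative Affect Schedule, as now.

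In section 3.10.1, keep 3.7 and label it as the conservative unadjusted figure.

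The cost is one degree of freedom per equation and a sentence or two of text. No new data, visits or participants are needed.
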